#### Part 3: clinical efficacy and cortical hemodynamic responses with optimal pressure

2.4.3

The experiment is divided into three groups, with healthy individuals without lumbocrural pain serving as the healthy control group, who receive intervention using optimal pressure parameters of the rolling manipulation. The protocol is 3 times per week, with one week as one treatment course, for a total of one course (3 interventions). This intervention is administered to investigate cortical hemodynamic changes induced by rolling manipulation with optimal pressure and to assess neuromuscular responses in healthy individuals with intact lumbar muscles, enabling a direct comparative analysis of brain functional and biomechanical responses to the identical manual intervention between healthy subjects and patients with lumbar muscle strain. fNIRS data are collected immediately before, during and after the 1st and 3rd interventions, while muscle tension and pressure pain threshold data are obtained before and after the intervention. Patients with lumbar muscle strain are divided into two groups: a case control group and a case intervention group. The case control group receives health education, whereas the case intervention group receives optimal-pressure rolling manipulation. The health education mainly covers posture management in daily life and work, lumbar protection, and guidance on appropriate physical activity and exercise, with participants’ questions addressed as needed. For both groups, the intervention protocol is 3 times per week, with one week as one treatment course, for a total of two courses. Muscle tension, pressure pain threshold, the Oswestry Disability Index (ODI) and VAS scores are assessed before intervention and immediately after the 1st, 3rd and 6th interventions, at the same detection positions as in Part 1. For the case intervention group, fNIRS data are additionally collected before, during and after the 1st and 3rd interventions. During fNIRS acquisition, participants remained in a prone position with the head and upper chest supported by soft pillows, and the forearms crossed under the forehead to provide additional head support. This posture ensured that the head remained in a relaxed and stable position. The rolling manipulation was applied exclusively to the lumbar region using a smooth, continuous rolling technique without abrupt flicking or plucking motions, thereby minimizing mechanical transmission to the head. The enrollment schedule and assessment protocol are shown in Table 2.

**Table 2 tab2:** Study schedule.

Stage	First visit	Pre-intervention	Intervention	Intervention	Post-intervention
Sign informed consent form	X				
Assign group number	X				
Lumbar spine AP & lateral X-ray	X				
Collect basic medical history					
General information	X				
Specialized examination	X				
Clinical DIAGNOSIS	X				
Confirm inclusion criteria	X				
Confirm exclusion criteria	X				
Efficacy observation part 1 trial		Pre-intervention	Intervention	Post-intervention	
Functional near-infrared spectroscopy (fNIRS)		X	X	X	
Muscle tension		X		X	
Pressure pain threshold		X		X	
Visual analogue scale (VAS)			X		
Part 2 trial		Pre-intervention	1st Post-intervention	2nd Post-intervention	3rd Post-intervention
Surface electromyography (sEMG)		X	X	X	X
Isokinetic muscle strength		X	X	X	X
Muscle tension		X	X	X	X
Pressure pain threshold		X	X	X	X
Visual analogue scale (VAS)		X	X	X	X
Part 3 trial		Pre-intervention	1st Intervention	3rd Intervention	6th Intervention
Oswestry disability index (ODI)		X	X	X	X
Functional near-infrared spectroscopy (fNIRS)			Before-during-after	Before-during-after	
Muscle tension		X	X	X	X
Pressure pain threshold		X	X	X	X
Visual analogue scale (VAS)		X	X	X	X
Study evaluation					
Treatment compliance	X				X
Adverse event assessment		X			X
Analysis of dropout reasons					X
Study completion summary					X
CRF statement review					X

To standardize the measurement conditions, all participants in Parts 1, 2, and 3 of the study were asked to maintain their usual daily activity level during the study period and to avoid additional strenuous physical activity. In addition, before each measurement, participants rested in a quiet environment for at least one hour to minimize the acute effect of physical activity on the baseline values.

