This study adopts a partial blinding method to control bias, and supplements standardized training for operators to reduce operation bias: At the participant level, in the crossover design of the second part, participants are unaware of the pressure level and intervention sequence. In Part 3, participant blinding to the type of intervention is not feasible because the case intervention group receives manual rolling manipulation whereas the case control group receives health education. Participants are not informed of the study hypotheses or the expected superiority of either intervention. Outcome assessors and statistical analysts remain blinded to group allocation. Data collection is performed by full-time researchers who do not participate in the interventions, and statistical analysts receive coded anonymous data; neither is aware of the grouping information. All operators receive unified standardized training for 3 times (2 h each time), including the calibration of manipulation pressure, frequency and operation position, and only pass the assessment (the consistency of manipulation parameters ICC>0.8) can they perform the intervention independently. Blinding is maintained by separating the intervention and data collection settings and formulating confidentiality protocols. The blind is only broken in accordance with procedures and documented in detail upon approval by the ethics committee in special circumstances such as the occurrence of serious adverse reactions in participants.

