The fluctuation ranges of the low, medium, and high pressure levels were calculated separately using the 95% confidence intervals: Fluctuation range (%) = (upper limit of 95%CI − lower limit of 95%CI) / (2 × mean) × 100%. The fluctuation range value (in Newtons) was then calculated as the mean multiplied by the fluctuation range percentage. For each pressure level, the lower limit of the interval was calculated as the mean minus the fluctuation range value, and the upper limit of the interval was calculated as the mean plus the fluctuation range value. The high-pressure level was applied strictly within the participant’s pain tolerance, and the operator’s physical capacity was also considered to avoid injury. After the pressure levels were determined, the Novel Pliance-X 32 Expert glove-type pressure distribution measurement system was used to measure the mechanical parameters of the rolling manipulation as an operational reference and to monitor standardization. The system is calibrated once a day before the operation to ensure the accuracy of pressure measurement. After the tuina pressure range is set, subsequent patients are strictly screened according to the “tuina pressure value range”determined by the experiment, and only subjects whose lumbar erector spinae bearing threshold fell within this range are included, and those beyond the range (too high/too low) are directly excluded.

A preliminary study was conducted before the formal trial to determine the washout duration. Six participants with lumbar muscle strain received a single session of rolling manipulation using clinically common parameters (4 kg, 120 times/min, 10 min). The root mean square (RMS) values of surface electromyography (sEMG) from the bilateral erector spinae were recorded before the intervention, immediately after the intervention, and on Days 3, 5, and 7 after the intervention. The RMS values increased immediately after the intervention, declined by Day 3, fell below the pre-intervention level by Day 5, and remained stable on Day 7. No statistically significant differences were observed between the pre-intervention values and those on Days 5 and 7, indicating that muscle activity had reached a stable state within 7 days. Accordingly, the washout period was set to 7 days (Table 1).

**Table 1 tab1:** RMS values of the bilateral erector spinae during the washout observation (*n* = 6).

Side	Baseline	Immediately after intervention	Day 3	Day 5	Day 7

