Oswestry Disability Index (ODI) (Part 3): The primary clinical outcome is the Oswestry Disability Index (ODI). The main analysis will compare the change in ODI from baseline to immediately after the 6th intervention between the case intervention group and the case control group. We expect a greater reduction in ODI in the case intervention group. ODI will also be assessed after the 1st and 3rd interventions to describe the course of clinical change. It covered 10 dimensions including pain intensity, activities of daily living, walking, sitting and sleeping, with 0–5 points for each dimension. The total score is converted into a percentage (0–100%), with a higher score indicating more severe dysfunction. Data are collected before intervention and immediately after the 1st, 3rd and 6th interventions to evaluate improvements in patients’lumbar function. If no more than 1 item is missing, the value is replaced by the average score of the completed items; if 2 or more items are missing, the data are regarded as invalid.

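### Table 2 assigns the group at the first visit and takes the baseline ODI only afterwards, so unblinded Part 3 patients may report the primary baseline knowing their arm

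*Protocol article*

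**What the plan says.** Section 2.4.3 names Table 2 as the schedule for enrolment and assessments. In that table the row "Assign group number" has a single mark, under First visit. In the Part 3 block the ODI row has its first mark under Pre-intervention, the column after First visit. VAS, pressure pain threshold (PPT) and muscle tension follow the same pattern.

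The text does not fix the order any further. Section 2.5.2 says of the ODI: "Data are collected before intervention and immediately after the 1st, 3rd and 6th interventions". That places the baseline before treatment, but not before allocation. Section 2.3.2 describes a stratified allocation of 46 patients, 23 per arm, by random number table, and gives no timing.

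The main Part 3 analysis is to "compare the change in ODI from baseline to immediately after the 6th intervention between the case intervention group and the case control group" (section 2.5.2). On blinding, section 2.3.2 says that in Part 3 "participant blinding to the type of intervention is not feasible because the case intervention group receives manual rolling manipulation", while the control arm receives health education. It adds that assessors and analysts are blinded and that participants are not told the hypotheses.

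**The concern.** A between-arm comparison of change scores relies on the baseline being independent of the allocation. Randomisation guarantees that only when the baseline is recorded before the patient can know the arm.

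The ODI asks about the patient's own pain, sleep and daily function. A patient who already knows whether hands-on treatment or education is coming may answer differently, through expectation or disappointment. That error would differ by arm and would sit inside the primary outcome. It could not be removed once the data are collected. Baseline adjustment would not remove it either, because the covariate itself would have been affected by allocation.

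**Working it through.** **1. Order of events.**

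| Item | Where | What is fixed |
|---|---|---|
| Group assignment | Table 2 | First visit only |
| First ODI, VAS, PPT, muscle tension (Part 3) | Table 2 | Pre-intervention, the next column |
| ODI timing in the text | Section 2.5.2 | Before intervention; not tied to allocation |
| Randomisation in the text | Section 2.3.2 | Method, no timing |
| Withholding the arm until baseline is complete | Not stated | – |

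Table 2 is thus the only place that sets the order, and it puts assignment first. This is also feasible in practice: the stratifiers, age and disease duration, can be taken from the first-visit history.

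**2. How a baseline shift reaches the estimate.** Let B and F be the mean baseline and final ODI, with subscript 1 for intervention and 0 for control. The estimate is D = (F1 − B1) − (F0 − B0). If knowledge of the arm moves B1 by b and the final scores by nothing, D moves by −b, that is, by the full b. If the final score moves by c in the same direction, the bias is −(b − c). A model that adjusts for baseline with slope s carries s × b rather than b. That is usually smaller, but it is not zero.

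**3. Scale.** The documents give no b, so 1 to 5 points is assumed for illustration. Section 2.8 gives a design difference of 10 and a standard deviation of 9, taken here as the standard deviation of the change. For 1 to 3 points, 1/10 = 10% and 3/10 = 30% of the design difference.

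**4. False-positive rate** with no true effect, two-sided 5% t test. Standard error = 9 × √(2/n): for n = 18, 9 × √(2/18) = 3.00; for n = 23, 9 × √(2/23) = 2.65.

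| Assumed shift b | n = 18 per arm | n = 23 per arm |
|---|---|---|
| 1 | 6% | 7% |
| 2 | 10% | 11% |
| 3 | 16% | 20% |
| 5 | 37% | 45% |

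**5. The plan's own sample size,** used here only to choose n. Inflating 18 for 20% attrition gives 18/0.8 = 22.5, so 23, as stated. The 18 itself does not follow from a difference of 10, SD 9, α = 0.05 and 80% power, which give 13 to 14 per arm two-sided; it corresponds to about 90% power. That discrepancy is separate, and the present point does not depend on it.

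**The case against.** **The table may not be a strict chronology.** Treatment compliance is also marked under First visit, before any treatment exists. Assignment is listed above the history rows that the stratification needs, so row order cannot be time order. A reader might infer from the row order that patients are assigned before eligibility is confirmed. The documents do not support this, because all those rows share one column. The column order remains. Pre-intervention is not said to be a separate visit or day, but it follows First visit.

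**Group number may be a code or a case/healthy label.** The row serves all three parts, including the non-randomised Part 1 and the healthy controls, and the term is not defined. This cannot be excluded. Against it, section 2.9 uses a different term, subject numbers, for participant identifiers. A reader might infer that Part 3 patients are told their arm at the first visit; no section says so. The objection reduces the point from an error shown to a risk left open.

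**Safeguards exist.** Blinded assessors do not protect a patient's own answers. Withholding the hypotheses does not conceal which treatment the patient will get.

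**Later ODI scores are exposed to expectation anyway.** That is true, and the Discussion concedes that nonspecific effects are not separated. It is no reason to let the baseline be exposed as well.

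**Part 2.** A reader might infer that Part 2 patients are assigned a sequence and then removed on their threshold, because section 2.4.2 says "those beyond the range (too high/too low) are directly excluded" and Table 2 first marks PPT at Pre-intervention. This is not supported. Section 2.4.2 words the threshold as a condition for inclusion and describes random assignment only afterwards. The PPT row is a repeated outcome and is not shown to be the screening check. Part 2 participants are also blinded to pressure level and sequence.

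**This is an article that condenses a fuller protocol.** When an allocation is opened is often left to the full document. Here, however, the article prints a schedule, and the order it prints is the unfavourable one.

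**Conclusion.** The point holds as a risk that the printed schedule permits, limited to the 46 randomised Part 3 patients. Three facts support it: assignment is placed before the first ODI, participants cannot be blinded, and the primary outcome is change from that ODI. No statement in the article closes the gap.

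It is not established that patients learn their arm before the baseline. The size and direction of any shift are unknown, and the figures above rest on an assumed shift, on unaffected later scores and on SD 9. Even so, a shift of 3 points, under a third of the design difference, would raise the two-sided 5% error to about 16% to 20%. Because the primary endpoint is involved and the data could not be repaired later, this should be settled before Part 3 enrolment.

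**What to change.** In Table 2, give the randomisation of the 46 Part 3 patients its own entry. Place it after eligibility is confirmed and after baseline ODI, VAS, PPT and muscle tension are recorded, immediately before the first session. Leave the case or healthy label for Part 1 and for the healthy controls at the first visit, where it belongs.

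In section 2.3.2, add one sentence saying that the Part 3 allocation is not opened until the baseline CRF page is complete.

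The cost is one table entry and one sentence, with no added visit, staff or procedure. The only practical effect is that arm-specific appointments are booked slightly later. If sites already work in this order, the change merely makes the table accurate.

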#### Randomization and blinding

2.3.2

Randomization is standardized in this study in combination with the design characteristics of the three parts of the experiment: The first part is a case–control observational study. After screening through strict inclusion and exclusion criteria, the case group (patients with lumbar muscle strain) and the control group (healthy people without lumbocrural pain) are selected from the eligible population by simple random sampling (15 cases in each group) to ensure sample representativeness, with no inter-group random allocation involved. The second part is a cross-over design study, in which 24 patients with lumbar muscle strain are divided into 3 groups (8 cases in each group) by complete randomization, receiving three sequences of rolling manipulation intervention with low-medium-high, medium-high-low and high-low-medium pressure, respectively. The third part is an interventional trial involving 69 participants in total. 46 patients with lumbar muscle strain are stratified by age and disease duration and then divided into a case intervention group (rolling manipulation intervention, *n* = 23) and a case control group (health education intervention, *n* = 23) by the random number table method; additionally, 23 healthy controls are selected by simple random sampling.

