Left (μV)	48.39 ± 19.42	54.37 ± 19.45*	49.64 ± 11.10	42.16 ± 8.67	41.16 ± 4.58
Right (μV)	45.46 ± 14.29	49.92 ± 23.50	48.16 ± 13.46	42.33 ± 11.37	43.10 ± 15.68

**p* < 0.05 vs. baseline. RMS: root mean square, reflecting the intensity of muscle activation. RMS increased immediately after the intervention, declined by Day 3, fell below the baseline level by Day 5, and remained stable on Day 7. The statistically significant increase immediately after the intervention was observed on the left side.

Participants were randomly assigned to one of three intervention sequences: low-medium-high, medium-high-low, or high-low-medium. Taking the low-medium-high sequence as an example, the procedures for the other two sequences (medium-high-low and high-low-medium) were identical, with the only difference being the order of pressure application.

First, surface electromyography, isokinetic muscle strength, muscle tension, pressure pain threshold and VAS indicators of the subjects’ bilateral lumbar regions are detected before the test; then, low-pressure rolling manipulation stimulation is applied to the subjects’ lumbar regions, with the intervention position at the bilateral L1-L5 lumbar erector spinae, repeated intervention from bottom to top for 10 min at 120 times/min; the operators are required to have more than 5 years of clinical experience in TCM tuina and hold a TCM practicing physician certificate. Finally, surface electromyography, isokinetic muscle strength, muscle tension, pressure pain threshold and VAS indicators of the bilateral lumbar regions are detected immediately after the rolling manipulation intervention.

Second, after the completion of the low-pressure rolling manipulation stimulation operation procedure and detection, the subjects enter a washout period. After the end of the washout period, the subjects receive medium-pressure rolling manipulation stimulation, and the operation procedure is the same as that of the low-pressure rolling manipulation stimulation, with the same detection methods and processes for medium and low pressure.

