### Participant safety

2.6

The inclusion and exclusion criteria are strictly implemented, contraindications are excluded through medical history collection, physical examination and imaging examination, and the informed consent form is signed with the right of voluntary withdrawal clearly stated. During the intervention, the VAS score is used to define the range of pain stimulation and rolling manipulation pressure, and the participants’ feelings are continuously monitored. If discomfort occurs, the intervention is immediately stopped and handled. Tuina operations are performed by professional doctors who have passed standardized training and hold relevant qualification certificates, in accordance with standardized procedures, and manipulation parameters are calibrated by relying on instruments. All detection equipment is regularly maintained, and qualified consumables are selected. An adverse event recording and emergency response mechanism is established. For better prevention and treatment, researchers detected any potential adverse events and recorded them truthfully on the Case Report Form (CRF).

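### Table 2 schedules adverse event assessment only before treatment and in its last column, so events between sessions rest on unscheduled report or late recall, and that last column does not fit every group

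*Protocol article*

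**What the plan says.** **Table 2 (study schedule).** The row "Adverse event assessment" sits in the study evaluation block. It is marked in the pre-intervention column and in the last column, with nothing between. The main header calls the last column post-intervention. The Part 2 sub-header makes it the assessment after the third session, the Part 3 sub-header makes it the 6th intervention, and the Part 1 sub-header leaves it empty because Part 1's own post-intervention visit is one column to the left.

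**Exposure in Part 2.** Section 2.3.2 has the three groups of eight "receiving three sequences of rolling manipulation intervention with low-medium-high, medium-high-low and high-low-medium pressure, respectively". Section 2.4.2 puts a 7-day washout between sessions. After each session, the listed measures are taken at once: "pressure pain threshold and VAS indicators of the bilateral lumbar regions are detected immediately after the rolling manipulation intervention".

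**Exposure in Part 3.** For both patient groups (section 2.4.3), "the intervention protocol is 3 times per week, with one week as one treatment course, for a total of two courses", which makes six sessions. Healthy controls are treated "for a total of one course (3 interventions"). The patients' clinical and muscle measures "are assessed before intervention and immediately after the 1st, 3rd and 6th interventions". No later contact is shown.

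**Section 2.6 (participant safety).** Participants' feelings are watched while the intervention is given, a recording and response mechanism is set up, and "researchers detected any potential adverse events and recorded them truthfully on the Case Report Form (CRF").

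**The concern.** The Introduction says that badly chosen pressure can bring risk, and gives safety as one reason for standardising the manipulation. The trial may therefore be read as showing which pressure is tolerated. That reading needs adverse events to be asked about in the same way after each exposure.

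The schedule does not do this. Biomechanical and pain measures are marked after every Part 2 session, while adverse events are marked once, after all three pressures. Soreness or a flare that begins a day or two after a session arises when no one is scheduled to ask about it. It is recorded only if the participant volunteers it, or if it is recalled at the end, after other pressures have been given. A low event count could then reflect how seldom the question was put.

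**Working it through.** No figure in the article needs reproducing here. The check compares the schedule with the exposure.

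**1. Post-baseline adverse event marks against sessions**

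Coverage = scheduled post-baseline marks / sessions given.

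| Group | Sessions | Post-baseline marks | Coverage |
|---|---|---|---|
| Part 2 patients | 3 | 1 | 1/3 |
| Part 3 patients, both groups | 6 | 1 | 1/6 |
| Part 3 healthy controls, main header | 3 | 1 | 1/3 |
| Part 3 healthy controls, Part 3 sub-header | 3 | 0 | 0/3 |

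By contrast, the five Part 2 measures in Table 2 (sEMG, isokinetic strength, muscle tension, pressure pain threshold, VAS) are each marked after all three sessions. The Part 3 patient measures are marked at the 1st, 3rd and 6th.

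**2. Recall interval in Part 2**

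With 7-day washouts, the time from the session in period k to the final assessment is about (3 − k) × 7 days: 14 days for the first session, 7 for the second and 0 for the third.

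| Sequence (n = 8 each) | 14 days | 7 days | 0 days |
|---|---|---|---|
| low-medium-high | low | medium | high |
| medium-high-low | medium | high | low |
| high-low-medium | high | low | medium |

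Of 24 × 3 = 72 sessions, 48 (two thirds) are followed by a scheduled adverse event assessment only after 7 or 14 days and at least one further pressure. The other 24 have it in the final column, with no scheduled observation afterwards. Each pressure is spread evenly: 8 sessions at each interval. With full retention the schedule does not favour a pressure. It weakens ascertainment for all three.

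**3. Recall interval in Part 3**

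Six sessions at three per week span up to about two weeks. The exact days are not stated.

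**4. Section 2.6 beside Table 2**

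The watch on participants' feelings is tied to the time of the intervention. The CRF sentence has no time limit, so it permits an event to be recorded at any point, but it names no occasion on which participants are asked. Table 2 names two. Read together, recording is open throughout and active assessment is scheduled only at the start and the end.

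**5. Whether the washout pilot adds evidence**

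Section 2.4.2 says RMS values "declined by Day 3, fell below the pre-intervention level by Day 5, and remained stable on Day 7". Change from baseline = (value / baseline − 1) × 100, from the Table 1 means (n = 6):

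| Side | Immediately | Day 3 | Day 5 | Day 7 |
|---|---|---|---|---|
| Left (baseline 48.39) | +12.4% | +2.6% | −12.9% | −14.9% |
| Right (baseline 45.46) | +9.8% | +5.9% | −6.9% | −5.2% |

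Only the immediate left-side rise is marked significant. Days 5 and 7 are reported as not significantly different from baseline.

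**The case against.** **Section 2.6 already covers recording.** Any potential event goes on the CRF, and nothing confines this to the two marked columns. Section 2.2.3 lists serious adverse reactions during the intervention as a ground for elimination or termination, and section 2.3.2 provides for unblinding when one occurs. The trial plainly expects to learn of harm before the end. This stands for events seen in a session or volunteered. It does not supply a scheduled question for events that arise between sessions.

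**Part 2 events can be attributed.** A reader might infer that they cannot be tied to a pressure. The documents do not support that: each period is one session at one pressure in a known order, 7 days apart. Section 2.4.2 repeats the same measurements in each period, so a flare lasting a week could show in the VAS before the next session. What is lacking is a routine adverse event question per period.

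**Healthy controls may well be assessed.** A reader might infer that 23 of 69 Part 3 participants (33%) have no adverse event visit after treatment. That follows only if the Part 3 sub-header governs the study evaluation rows. Under the main header the column is post-intervention, and it also holds the dropout analysis and completion summary, which suggests the end of participation. Healthy controls and early stoppers would then have the visit. The table is ambiguous, and a gap is not shown.

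**The article is condensed.** A fuller protocol or CRF may carry per-visit questions. This limits the weight of the point. It does not remove it, because the article prints a schedule, and that schedule does not match its own safety section.

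**Conclusion.** The point holds in a limited form. The stated schedule gives one post-baseline adverse event assessment for three Part 2 sessions and one for six Part 3 patient sessions. Events in washout or between sessions depend on unscheduled report or on recall of up to about 14 days. The last column has different meanings across the main header and the sub-headers, and does not fit the three-session healthy controls or Part 1 without interpretation.

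The consequence is for how safety can be described. The choice of pressure is not affected: section 2.4.2 makes it on sEMG and other biomechanical findings within the VAS tolerance range, and plans no adverse event comparison between pressures.

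A reader might also take the pilot as evidence of delayed harm. It is not. It measured sEMG RMS in six people, reports no adverse events, found no significant difference at Days 5 and 7, and on the right side the Day 7 change is smaller than the immediate one.

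The conclusion assumes that the Table 2 columns align as they appear in the article, that each washout lasts 7 days, and that no fuller schedule elsewhere overrides the printed one.

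**What to change.** Reconcile Table 2 with section 2.6:

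- Mark adverse event assessment before and after every session that already takes place, in all parts and all groups, including the health education sessions. That is 6 question points in Part 2, 12 for Part 3 patients and 6 for healthy controls, in place of the present 2.
- In Part 2, code each event to the period and the pressure most recently given.
- Define the final mark as the last session received: the 3rd intervention for healthy controls, Part 1's own post-intervention column, and the last attended session for anyone who stops early.

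A short contact after the last session would cover the period that is now unobserved. It is optional, and the point does not depend on it.

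The cost is a few minutes per session and an amendment to Table 2 and the CRF. No extra visit is needed, and treatment, randomisation and sample size are unchanged.
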